**Patient partners**

[name]

[name] Synopsis

| Title of clinical trial |  | Multicentre prospective single-blind wait-list randomised controlled trial of the clinical value and cost-effectiveness of an online physical and emotional wellbeing resource for the improvement of health-related quality of life in people with chronic kidney disease: The Kidney Beam Trial |
| --- | --- | --- |
| Protocol Short Title/Acronym |  | **The Kidney Beam Trial** |
| Trial Phase if not mentioned in title |  | Phase IV |
| Sponsor name |  | King’s College Hospital NHS Trust |
| Chief Investigators |  | [name] |
| ClinincalTrials.gov number |  | NCT04872933 |
| REC number |  | 21/LO/0243 |
| Medical condition or disease under investigation |  | Chronic Kidney Disease (CKD) |
| Purpose of clinical trial |  | This is a multi-centre single-blind waitlist randomised controlled trial (RCT) that will examine the clinical value and cost-effectiveness of an online physical and emotional wellbeing resource for the improvement of health-related quality of life in people with CKD. |
| Trial objectives |  | 1. To assess the clinical value and cost-effectiveness of an online physical and emotional wellbeing resource for the improvement of health-related quality of life in people with CKD. 2. To assess healthcare utilisation and associated cost of an online physical and emotional wellbeing resource for the improvement of health-related quality of life in people with CKD. 3. To assess mental health, physical function, physical activity, patient activation, fatigue, and clinical measures. 4. To explore the acceptability of the trial procedures and the BEAM platform (short and longer-term). |
| Trial Design |  | An investigator-led multicentre waitlist RCT of participants with CKD |
| Primary outcome measure |  | Mental Composite Score (MCS) of KDQOL-36 quality of life questionnaire at 12 weeks. |
| Main secondary outcome measures |  | - *EQ5D-5L questionnaire* - *Patient Activation Measure (PAM-13)* - *The Patient-Health Questionnaire-4* - *Chalder Fatigue Questionnaire -- physical and mental fatigue* - *Work and Social Adjustment Scale (WSAS)* - *Functional capacity (sit-to-stand 60 to assess lower limb function)* - *Global Physical Activity Questionnaire (GPAQ)* - *Quality of life (KDQOL-36 physical composite score, energy/fatigue, burden of kidney disease, role physical, physical functioning, mental health, bodily pain, role emotional, social functioning, general health)* - *Patient engagement with the digital platform* - *Qualitative exploration of acceptability and participant experience* - *Healthcare utilisation* - *Adverse events* |
| Sample Size |  | 304 participants |
| Summary of eligibility criteria |  | Patients with established CKD  Aged 18 years+  Patients who are naïve to Kidney Beam intervention and who have not participated in a structured exercise programme in the prior 3 months |
| Intervention |  | Kidney Beam digital health intervention platform – physical activity and emotional wellbeing via live and on demand video content |
| Active comparator product(s) |  | Waitlist control group |
| Maximum duration of treatment of a  subject |  | 3-month intervention, 6-month follow-up (9 months in total) |
| Project costs |  | £159,872 |

### Glossary of Terms

| **AE** | Adverse event |
| --- | --- |
| **AT** | Aerobic training |
| **CKD** | Chronic Kidney Disease |
| **CTO** | Clinical Trials Office |
| **CRP** | C-Reactive Protein |
| **eGFR** | Estimated glomerular filtration rate |
| **GCP** | Good Clinical Practice |
| **Hb** | Haemoglobin |
| **ICF** | Informed consent form |
| **ICH** | International Conference on Harmonisation |
| **HRA** | Health Regulatory Agency |
| **QoL** | Quality of life |
| **RCT** | Randomised Controlled Trial |
| **REC** | Research Ethics Committee |
| **RT** | Resistance training |
| **SAE** | Serious adverse event |
| **STS60** | Sit-to-stand 60 |
| **UK** | United Kingdom |

**21 References …………………………………………………………………………………30**

### 3. Background & Rationale

Physical inactivity and poor mental health are very real concerns for people living with kidney disease, and they report multiple symptoms that impact upon the physical component of health-related quality of life (HRQoL) (1). A decrease in the physical component of HRQoL is independently associated with mortality and morbidity (2,3). In people living with end stage kidney disease (ESKD), systematic reviews indicate that a range of exercise training interventions improve physical function and alleviate disability symptoms (4-18). The physical component of HRQoL can be targeted with interventions to enhance physical activity, however people living with kidney disease are still not routinely offered specialist physical activity or mental health support in the NHS. Fatigue is a complex array of symptoms described as ‘extreme and persistent tiredness, weakness or exhaustion-mental, physical, or both’ (19-21). Fatigue is present across the full spectrum of chronic kidney disease (CKD), affecting patients not yet requiring renal support. It is a common complaint in ESKD, affecting from 42 to 89 percent of patients, and persists in those who subsequently received a renal transplant (21,22). In ESKD, fatigue has huge repercussions on HRQoL, further impairing patients’ daily functioning, motivation, social engagement (4,23-26), and contributing to poorer sleep quality and increased bodily pain (23,24,27). There is also evidence to suggest that fatigue may contribute directly to clinical outcomes, increasing the risk of cardiac events and mortality (25). A UK-wide MDT survey revealed significant barriers to the provision of exercise counselling including; a lack of available exercise professionals and facilities and difficulty with the wide geographical reach of the CKD patient population who attend tertiary care clinics, as well as a lack of funding (29). A recently published joint statement from The Centre for Mental Health and Kidney Research UK highlighted the very real need for improved access to services that promote physical and mental wellbeing for people living with kidney disease (30). This has only become more urgent as a result of the Coronavirus pandemic, which has further reduced the physical activity levels of those living with CKD and undoubtedly negatively influenced the quality of life of people living with CKD, many of whom have been required to shield during this time.

Kidney Beam [https://beamfeelgood.com/home](about:blank) is a new wellbeing digital health intervention platform that was developed, and launched, to help people with kidney disease manage their physical and mental health through the Coronavirus 2019 (COVID-19) pandemic, resulting lockdown and beyond. Early in the COVID-19 pandemic, people with CKD were identified as being at an increased risk of more severe infection from this virus (31) and a mortality rate of 15.2% mortality rate, much greater than the general population was reported in the UK (32). Consequently, these individuals were advised to take extra precautions to minimise their risk of exposure (31) which, in the UK, resulted in re-classification of these individuals as ‘extremely clinically vulnerable’ to COVID-19 on Thursday 23^rd^ April 2020 and shielding at home. Kidney Beam was developed to offer people to help kidney patients manage their physical and mental health through the Coronavirus pandemic lockdown and beyond. Kidney Beam offers people living with kidney disease a way to improve their physical activity and boost their mental health through live and on demand movement classes and expert educational videos, while remaining in their own home. The free online service was a collaboration between King's College Hospital, Kidney Research UK and Beam, a digital health intervention platform supporting people with health conditions to stay physically active. Kidney Beam is led by specialist kidney professionals, including renal physiotherapists and renal counsellors, from a number of different NHS Trusts and backgrounds, as well as people living with kidney disease. The resource is aimed at anyone over 18 with any ability, any kidney condition, and at any stage of kidney disease. The 6-month pilot will end on the 30^th^ November 2020. The team are seeking funding to extend the free access to the resource for a further 12-months while the team evaluate the clinical value and cost effectiveness of the digital health intervention platform. The Kidney Beam project has been highlighted as a key project that will be supported by the Renal Transformation Plan, having already been discussed and reviewed by the Renal Clinical Reference Group (CRG) and NHS England for potential commissioning following the 12-month study.

Our patient advisory group, who have been integral to shaping the Kidney Beam digital health intervention platform, strongly recommended that any resource include a variety of exercise classes for patients to do at home, and emotional support from healthcare professionals. Kidney Beam has already attracted in excess of 700 sign-ups from across the UK and has been well-received by people living with kidney disease, and the renal healthcare professionals alike. As an online intervention, Kidney Beam, has the potential to overcome the well documented geographical access barriers to specialist physical activity and emotional support services for patients with CKD (33,34) and represents an efficient use of limited resources in a financially unstable NHS. Indeed, the NHS 5-year forward view and the Carter report highlight the need to look at digital solutions as a way to promote efficiency in the NHS (35,36).

### 4. Trial Objectives and Design

### 4.1. Trial Objectives

To conduct a multi-centre waitlist RCT that will examine the clinical value and cost-effectiveness of an online physical and emotional wellbeing resource for the improvement of health-related quality of life in people with CKD. The study will assess the clinical value of the Kidney Beam digital health intervention platform, as assessed by the Mental Component Score (MCS) of the KDQOL-36 questionnaire, in people living with CKD. The study will also examine whether the Kidney Beam digital health intervention platform is cost effective, and can improve mental and physical health, physical function, fatigue, and patient activation.

**PRIMARY OBJECTIVE**

1. To assess the clinical value of the Kidney Beam digital health intervention platform, as assessed by the MCS of the KDQOL-36 HRQoL questionnaire.

**SECONDARY OBJECTIVES**

1. To assess cost effectiveness, mental and physical health, physical function, quality-of-life, patient activation, and fatigue in people living with CKD.
2. To explore the perceptions of people living with CKD in relation to Kidney BEAM, and their experience of using the platform

Specifically, we propose to examine whether a physical and emotional wellbeing package – Kidney Beam - can improve the mental composite score of the KDQOL-36 QoL questionnaire.

The results of this trial will provide data to support the clinical commissioning of the Kidney Beam digital health intervention platform.

**4.1.1 Primary outcome measure**

Mental HRQoL as measured by MCS of the KDQOL-36 at 12 weeks.

**4.1.2 Main secondary outcome measures**

- *Patient activation measure (PAM-13)*
- *Chalder Fatigue Questionnaire -- physical and mental fatigue*
- *Patient Health Questionnaire-4 (PHQ-4)*
- *Functional capacity (sit-to-stand 60 to assess lower limb function)*
- *Quality of life (KDQOL-36 physical component score (PCS), energy/fatigue, burden of kidney disease, role physical, physical functioning, mental health, bodily pain, role emotional, social functioning, general health)*
- *Global Physical Activity Questionnaire (GPAQ)*
- *Clinical Frailty Score*
- *Work and Social Adjustment Scale*
- *Qualitative exploration of intervention and trial acceptability and participant experience*
- *Adverse events*
- *Kidney Beam platform metrics (physical activity minutes, engagement)*

**4.2 Trial Design**

An investigator-led multicentre single-blind waitlist randomised controlled trial (with nested pilot study) of participants with established chronic kidney disease (CKD).

**Nested pilot study**

The study will adopt a nested pilot design to preliminarily assess trial and intervention feasibility. To assess this, a range of *a priori* progression criteria based on a traffic light system will be utilised to determine if the study should be halted (red), changes to the design or intervention considered (amber) or is considered feasible and progress to the full trial (green). These progression criteria will be co-developed with a panel of experts and stakeholders including patients, healthcare professionals and researchers.

**Feasibility outcomes**

At 12 weeks, outcomes pertaining to the feasibility of the intervention and trial will be assessed following each phase of the trial. This will be for the overall trial sample at 12 weeks, and for the first 3 external sites that are opened in the study.

o Recruitment rate

The feasibility of recruitment and interest of patients is an essential component of whether the full trial is feasible. The number of eligible patients and number of consented will be recorded. Monthly recruitment rate and the time taken to recruit 25%, 50%, 75%, and 100% patients will be recorded.

o Acceptability of randomisation and assessment procedure

Acceptability of randomisation and procedures, and by measuring loss to follow-up and by exploring patient’ views about their participation in the research

o Adherence to intervention

Adherence will be assessed by the completion of the exercise sessions. We will also assess patterns and frequency of programme usage.

o Attrition rate

The number of drop-outs (attrition rate) in the study will be recorded.

o Missing data

Quantity of missing data (e.g., questionnaire completion rate, outcome measures not completed)

o Trial and intervention acceptability

This will be attained through qualitative interviews in a sub-set of patients.

**Progression criteria**

The decision regarding trial feasibility will be made using a composite assessment of both quantitative and qualitative data based on a traffic light system (‘green’ (go), ‘amber’ (amend), and ‘red’ (stop) using pre-defined criteria (37,38).

The main criteria contributing to this system are:

o recruitment rate (patients consented/approached)

o adherence to intervention

o acceptability of randomisation and assessment procedures

o attrition rate

o missing data

o The opening of secondary research sites to commence the trial

Relative 'green’, ‘amber’, and ‘stop’ criteria will be formed prior to the intervention through our group’s previous experience, discussion with collaborators and patient advisory members, and other literature (39). Analysis against the stop-go criteria will be undertaken at the end of the pilot phase (40).

Assessments will be performed at baseline, and after 12 weeks, and will compare the Kidney Beam digital health intervention platform with a waitlist control group.

**BEAM trial progression criteria at 12 weeks, for internal feasibility study**

**Eligibility**

No set progression criteria, but each centre will be required to report the numbers in each population of interest (pre-dialysis, PD,HD, transplant) who have been screened, and the proportion recruited to ensure that a representative population is being targeted.

**Recruitment:**

On the basis of 8 centres, aiming to recruit n=304 within 9 months.

Go:

- 15 participants recruited within 12 weeks per centre.

Amber

- Less than 15 recruited per centre, but other centres are able to make up the shortfall

Stop

- 3 centres are unable to open to recruitment

**Acceptability of randomisation:**

The characteristics (and the proportion by group) of participants withdrawing post randomisation will be captured to determine the acceptability of the waitlist design.

**Intervention acceptability:**

The proportion of participants attending live or on-demand classes via the Kidney Beam platform at 12 weeks will be reviewed.

Go:

- Engagement with at least one BEAM class per week for 70% participants

Amber:

- Engagement with at least one BEAM class per week for 60% participants

Stop:

- Engagement with at least one BEAM class per week in<50% participants

**Outcome acceptability:**

For the primary outcome (KDQoL):

Go:

- At least 80% completion rate

Amber:

- At least 70% completion rate

Stop:

- Less than 60% completion rate

**Retention**

Initial dropout rate will be considered as not all participants will have completed the programme by the end of the 12-week pilot phase

Go:

- Less than 20% drop out rate

Amber:

- Less than 40% drop out rate

Stop:

- More than 50% drop out rate

### 4.3 Trial Flowchart

**INCLUSION CRITERIA**

1. Patients with established CKD
2. Men and women aged 18yrs+
3. Access to a wifi-enabled device
4. Able to understand written English language
5. Written or virtual informed consent

**SELECTION OF PARTICIPANTS**

CKD patients

Age 18yrs+

- **4.4 Study procedures (all remote): Screening to 12 weeks**

**EXCLUSION CRITERIA**

1. Weight < 50kg
2. Active infection
3. Participation in structured exercise programme or Kidney Beam resource in prior 3 months
4. Uncontrolled arrhythmias
5. Unstable angina or heart attack within the last 3 months
6. Persistent uncontrolled hypertension (systolic blood pressure >180 mm Hg or diastolic blood pressure >110 mm Hg)
7. Recent (within the last 3 months) stroke or transient ischaemic attack
8. Receiving palliative care for advanced terminal cancer
9. Patients with peripheral vascular or musculoskeletal disease, who the investigator deems unable to carry out a physical activity intervention.
10. Any other health condition considered by the local Principal Investigator in which physical activity will be contraindicated.
11. Insufficient understanding of the trial

**RANDOMISATION/BASELINE Assessment Visit**

Not for

COVID

Sub-study

Post COVID functional assessment tool

NO

YES

History of COVID

**12 WEEK Assessment Visit**

**12 weeks:**

**Kidney Beam intervention**

**Non-waitlist**

Not for

COVID

Sub-study

Post COVID functional assessment tool

NO

YES

**12 weeks Kidney Beam intervention**

**12 WEEK Assessment Visit**

**12 weeks:**

**Normal routine care**

History of COVID

**Waitlist**

**SCREENING**

Inclusion and Exclusion criteria

**Patient Information Sheet** **/ Consent Form**

Patient Information Sheet given to potential patients.

Consent form signed.

| PROCEDURE | | Screen Visit | End of 12 week pilot phase | Baseline/Randomisation Visit | Week 12 Visit | 6-month follow-up |
| --- | --- | --- | --- | --- | --- | --- |
| Patient information and informed consent | | X |  |  |  |  |
| Inclusion / Exclusion criteria | | X |  |  |  |  |
| Demographic data and medical history | | X |  |  |  |  |
| Height, weight, BMI, Clinical Frailty Scale | |  |  | X | X |  |
| **Vital signs (Blood pressure & heart rate) | |  |  | X | X |  |
| **Full blood count | |  |  | X | X |  |
| **Creatinine, CRP, eGFR, Hb, IL-6, Albumin from routine bloods | |  |  | X | X |  |
| Fatigue Severity Score (Chalder Fatigue questionnaire) | |  |  | X | X |  |
| Functional impairment (WSAS Questionnaire) | |  |  | X | X |  |
| Quality of life (KDQOL-36 and EQ5D-5L) | |  |  | X | X | X |
| Functional capacity (STS60) |  | |  | X | X |  |
| Global Physical Activity Questionnaire (GPAQ), and Physical Health Questionnaire (PHQ9) and additional questions on meeting current physical guidelines. |  | |  | X | X |  |
| Patient Activation Measure |  | |  | X | X |  |
| Qualitative Interview |  | | X |  | X |  |
| Adverse Events |  | |  | X | X |  |
| Kidney Beam platform metrics (PA mins and engagement) |  | |  |  | X | X |
| Healthcare utilisation questionnaire |  | |  | X | X | X |
| ***Post-COVID functional assessment tool questionnaire |  | |  | X | X | X |
| ****Digital health literacy screening tool | X | |  |  |  |  |
| ^*****^Hand grip Strength |  | |  | X | X |  |

** This procedure will only be a retrospective review of most recent available routine blood tests results and vital sign measurements. Results with date will be recorded by the study team. No new blood test will be collected from patient.

*** Only patients who had history of COVID at time of consent will be assessed for Post-COVID functional assessment tool questionnaire at Baseline.

****Only a sub set of patients from Kings College Hospital.

^*****^Only in a subset of patients at Newcastle NHS Trust

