**7.3 Baseline / Randomisation Visit(s)**

The baseline/randomisation visit must occur no more than 4 weeks after the patient has successfully passed screening. The assessments will be conducted virtually by a research assistant.

The data as detailed below and in the study procedures table (Section 4.4) must be collected and all required procedures performed during the baseline/randomisation visit.

- Concomitant medications
- Vital signs (Blood pressure & heart rate) (Retrospective review of most recent reported measurements)
- Height, weight, BMI
- Patient Activation Measure (PAM-13)
- Clinical Frailty Scale
- Physical Health Questionnaire-4 (PHQ-4)
- Fatigue severity score (Chalder Fatigue Questionnaire)
- Work and social adjustment scale (WSAS Questionnaire)
- Functional capacity (sit-to-stand 60 to assess lower limb function)
- Global Physical Activity Questionnaire (GPAQ)
- Are you meeting current physical activity guidelines?
- Quality of life (KDQOL-36 and EQ5D-5L)
- Routine blood tests – Creatinine, Haemoglobin, CRP, IL-6, Albumin

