**7.5 Week 12 Appointment**

The week 12 appointment must occur 12 weeks (+4 weeks) after the patient has had their baseline appointment.

The data as detailed below and in the Trial Flowchart must be collected and all required procedures performed during the 12-week appointment.

- Concomitant medications
- Vital signs (Blood pressure & heart rate) (Retrospective review of most recent reported measurements)
- Height, weight, BMI
- Patient Activation Measure (PAM)
- Clinical Frailty Score
- Physical Health Questionnaire-4 (PHQ-4)
- Fatigue severity score (Chalder Fatigue Questionnaire)
- Functional Impairment (WSAS Questionnaire)
- Functional capacity (sit-to-stand 60 to assess lower limb function)
- Global Physical Activity Questionnaire (GPAQ)
- Are you meeting current physical activity guidelines?
- Quality of life (KDQOL-36 and EQ5D-5L)

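### Week-12 bloods and vital signs need not postdate randomisation, so a participant not retested since baseline has the baseline record entered twice

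*Protocol*

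**What the plan says.** The study procedures table (Protocol, Section 4.4) marks vital signs, full blood count and the row "Creatinine, CRP, eGFR, Hb, IL-6, Albumin from routine bloods" at both the baseline/randomisation visit and the week-12 visit. One footnote governs all three rows: "This procedure will only be a retrospective review of most recent available routine blood tests results and vital sign measurements". It adds "Results with date will be recorded by the study team" and "No new blood test will be collected from patient".

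Sections 7.3 and 7.5 repeat the rule for vital signs in the same words at both visits: "Vital signs (Blood pressure & heart rate) (Retrospective review of most recent reported measurements". For bloods the two sections differ. Section 7.3 lists "Routine blood tests – Creatinine, Haemoglobin, CRP, IL-6, Albumin" at baseline, while the Section 7.5 list for week 12 contains no blood tests.

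The only timing rule at week 12 concerns the visit: "The week 12 appointment must occur 12 weeks (+4 weeks) after the patient has had their baseline appointment". It limits when the appointment takes place, not how old the record may be.

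The measures enter the objectives through the third trial objective in the synopsis: "To assess mental health, physical function, physical activity, patient activation, fatigue, and clinical measures".

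**The concern.** A week-12 value should describe the participant after 12 weeks of intervention or waiting. Under this rule it describes whatever routine care last recorded. If there has been no routine test since baseline, the latest record is still the one entered at baseline. A site that follows the protocol exactly enters it a second time.

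Such a participant contributes a change of exactly zero whatever actually happened. If repeats occur equally in both arms, they pull the difference between arms towards zero. Dilution would also differ across the pre-dialysis, peritoneal dialysis, haemodialysis and transplant groups if they are monitored at different frequencies. A report of no change in CRP, haemoglobin or blood pressure would then partly reflect the collection rule.

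The protocol does set time limits elsewhere: baseline within 4 weeks of passing screening, re-consent after 3 months, and 4 weeks' tolerance on the week-12 and 6-month visits. The routine records have no such limit.

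**Working it through.** The protocol states no figure on this point, so there is none to reproduce. The check has a textual part and an illustrative part.

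**Text.** Four provisions are read together.

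1. Week-12 vital signs and bloods are scheduled (Section 4.4 table).
2. The source is the latest routine record (Section 4.4 footnote; Sections 7.3 and 7.5 for vital signs).
3. No new blood sample is taken (Section 4.4 footnote).
4. No section sets a maximum age, requires a date after randomisation, or says what to enter when nothing newer exists. Section 8 adds only that laboratory parameters are reviewed at each visit.

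From 1 to 4, a participant with no routine test between the two visits has one eligible record, and it is entered at both. A record made shortly after randomisation would also qualify as week 12, which is why a window is needed as well as a post-randomisation condition.

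**Size.** Inputs:

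- Gap between visits, G: 12 to 16 weeks (Section 7.5).
- Mean interval between routine tests, I: not in the protocol; assumed range 4 to 52 weeks.

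Share of participants with no new record, f:

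- regular testing, visit at a random point in the cycle: f = max(0, 1 − G/I)
- irregular testing (Poisson): f = exp(−G/I)

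For example, with G = 12 and I = 26, regular testing gives 1 − 12/26 = 0.54 and irregular testing gives exp(−12/26) = 0.63.

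| I (weeks) | G = 12, regular | G = 12, irregular | G = 16, regular | G = 16, irregular |
|---|---|---|---|---|
| 4 | 0% | 5% | 0% | 2% |
| 12 | 0% | 37% | 0% | 26% |
| 16 | 25% | 47% | 0% | 37% |
| 26 | 54% | 63% | 38% | 54% |
| 52 | 77% | 79% | 69% | 74% |

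**Effect on a comparison.** If repeats are independent of arm and of effect, the expected between-arm difference in change is multiplied by (1 − f). With f = 0.54, 46% of the true difference remains; with f = 0.77, 23% remains.

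**Sensitivity to the random-phase assumption.** Section 6.3 says potential participants are identified at routine clinic visits, though letter and telephone are also allowed. Suppose bloods were taken and screening passed at that clinic visit, which is an assumption. Baseline would follow within 4 weeks, and with I = 26 the next routine test would fall at least 26 − 4 = 22 weeks after baseline. That is beyond the 16-week limit, so nearly all such participants would repeat. The table is therefore an illustration, not an estimate.

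**The case against.** The strongest reply is that the dates are recorded. Repeats and pre-randomisation records can be found at analysis, and the choice of which dated record counts for a visit is commonly left to the statistical analysis plan, which is not shown. This stands in part. It means the problem can be repaired and that zero change need not reach the final analysis. It does not remove the point, because the protocol itself fixes which record a site enters as week 12, and that rule gives a wrong value for anyone not retested.

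The second reply is that little depends on these measures, and this stands. Bloods and vital signs are in neither list of main secondary outcomes (synopsis and Section 4.1.2), and the objectives in Section 4.1 do not mention them. Their only anchor is the undefined term clinical measures in the synopsis. The change analysis in Section 10.3 names the mental composite score and other outcome measures, and does not clearly include them.

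The third reply is that recording untimely values as missing swaps dilution for selective missingness in infrequently monitored patients. This also stands as a cost. However, a repeated baseline record carries no week-12 information, so calling it missing loses nothing real and makes the gap visible.

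A reader might also infer that a finding of no change would be misread as evidence of no harm. The protocol does not support that. Section 9.1 bases safety on serious adverse events, hospitalisation and infection episodes, and no section uses change in bloods or vital signs as safety evidence.

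**Conclusion.** The point holds as a defect in the collection rule, with high confidence on the text. Week-12 vital signs and bloods are not required to postdate randomisation, so a participant not retested shows zero change by construction and any between-arm difference in change is diluted by the share of repeats.

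The size is unknown. Across the assumed intervals and both testing patterns the share runs from 0% to 79%. It is tempting to conclude that many participants would be affected, but the protocol gives no testing frequency and frequent regular testing would bring the share to about zero. It is equally tempting to say that the third objective could not be answered for these measures. The supportable statement is weaker: the evidence on them would be diluted unless the recorded dates are used.

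The primary outcome, the listed secondary outcomes and the sample size are unaffected. This is a correction worth making, not one on which the trial depends.

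**What to change.** In the Section 4.4 footnote and in Section 7.5:

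- Count a value as week 12 only if it is dated after randomisation and falls within a date window that the sponsor states. The protocol offers no basis for a particular width, so the sponsor must choose it.
- Otherwise record the value as missing.
- Never enter the same dated record at both visits; a database edit check on the dates already collected would enforce this.
- Report the number missing by arm and by CKD group.

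In the same edit, reconcile the procedures table, which schedules full blood count and the blood panel at week 12, with the Section 7.5 list, which omits them.

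The cost is a revised footnote, a matching line in Section 7.5 and one edit check, with no new tests. The downside is more missing values, concentrated in less frequently monitored patients. An analysis of the remaining values would therefore lean towards those monitored more often, and the counts by CKD group would show how far.
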